**Covariates**				
Depressive and anxiety symptoms	Self-report of depressive symptoms and anxiety symptoms in the last week [59]	SAQ	IG, CG	t0, t3, t6, t12, t18
Osteoporosis risk status	German version of osteoporosis risk test [60]	SAQ	IG, CG	t0, t3, t6, t12, t18
Back pain	Three months retrospective questionnaire on the severity of chronic back pain [61, 62]	SAQ	IG, CG	t0, t3, t6, t12, t18

*APS* Physician-Partner-Service, *CG* Control group (regular care), *CRF* Case report form (on-site CRF will be provided by study staff, exercise specialists and physician, if applicable; *eCRF* Electronic case report form), *ECG* Electrocardiogram, *HEPA Index* Health enhancing physical activity, *IDB* Insurance data base, *IG* Intervention Group *MultiPill-Exercise*, *PE* Physical exercise, *SAQ* Self-administered (online) questionnaire, *t* Collections points, *m* Minus. 0, 3, 6, 12, 24: month of collection point related to baseline (t0), *QI* Qualitative interview

The initial two weeks will focus on familiarization with exercise and motor learning. The participants will also be introduced to training at the study sites including strength training on the weight-machines and ergometers and tread-mills for endurance training, where applicable. For functional strength training at home, videos including whole body exercises in different starting positions and difficulty variants will be made available to participants by logging into an online platform from the health insurance company. The following four weeks (week 3–6) will emphasis basic endurance training (cardio-vascular training, machine-based and functional strength training). For the endurance training, different training methods will be introduced, such as the continuous method and high intensity interval training. Machine-based strength training in this phase is performed as strength endurance training. The subsequent continuation training (week 7–10) will carry on the goals of the previous weeks. However, by reducing the number of repetitions and increasing the intensity, the machine-based training will be changed to a targeted muscle-building workout. Functional training sessions will be supplemented by exercise group offers close to everyday life ("movement teaser") that focus on different motives for exercise participation (health, aesthetic, competition, contact, enjoyment, distraction, nature etc.). The final maintenance training of the first phase (week 11–12) is designed to promote independent exercise participation and will include only one supervised training session/week.

During the second 12 weeks, the activities of the first phase are to be maintained. Participants will continue machine-based training sessions 1x/week at the study sites. The endurance sessions can be done independently home-based or in a group. Cooperation with local sport clubs and gyms or else will be encouraged.

Each participant will receive a weekly individualized training plan in both phases of the intervention, which will include training parameters in addition to the scheduled training sessions. For endurance training, heart rates and watts are added individually, calculated from the performance diagnostics. Strength training will be regulated by the Borg scale (0: no effort- 10: maximum possible effort) (details see Additional file 3).

(2)In order to strengthen the effect and action knowledge of the participants, participant education sessions of 30 min each will be held, delivering theoretical and practical knowledge on the basics of training sciences, nutrition (healthy and anti-inflammatory diet), themes to enhance motivation and volition [63], motives and goals of PA [23, 52] and PA in daily life [64]. While five theory sessions will be scheduled for phase 1, phase 2 will include a nutritional booster session (anti-inflammatory diet). A theory–practice link is always strived for. 

(3)Three individual counselling sessions (30 min each) using further behavioral change techniques will take place in phase one. The individual counselling to enhance regular sport participation will be conducted by a guide; an exercise specialist who will also act as a personal contact person. The guide will be briefed on the diverse behavior change techniques included (MoVo-Lisa concept [65], the exercise counseling approach based on motives and goals in exercise and sport (COMET) [23], including 5A’s [66], and techniques from Motivational interviewing [67]). The personal guide will also be responsible for weekly feedback on the participant’s training logs. Phase two includes two individual counselling appointments (anti-inflammatory diet and COMET). The counselling sessions are based on the individual training diaries, the participant’s feedback on the movement teasers and the individual results of the assessment of the Bernese motive and goal inventory in exercise and sport (BMZI) [52]. The counselling on nutrition and dietetics will build on two seven-day nutrition logs (these are kept after each of the nutrition lectures) and will be evaluated and discussed with a nutritionist from the insurance company.

All individual and group sessions on-site will be conducted by exercise professionals, employees of the statutory health insurance company at each of the study sites. Several exercise specialists and nutritionists from the statutory health insurance company will be trained in advance on the *MultiPill-Exercise* intervention design. Only trained exercise professionals will also act as guides in the intervention. The exercise specialists will receive a comprehensive manual for delivering the exercise intervention to enable standardization across study sites.

### Standard Care (CG)

The standard care of statutory health insurance company offers every insured person the opportunity to participate in health offers, provided and conducted by employed professionals from the health insurance company, free of charge. For a more detailed information of the German health care see Struckmann, Boerma [68].

Participants of the CG are requested to select from the standard care offers of the statutory health insurance company. Potential offers are in the field of nutrition, exercise and special DMPs, general health and ‘fit and active’. The exercise offers last 8–12 weeks. Participants of the CG will be provided with options by an exercise specialist of the insurance company and will then be able to enroll in the selected offers. Over the study period, participants can attend two different offers, as foreseen in regular care. The combination and choice of offers can be freely arranged according to the participants' own preferences. An exception applies to participants with a physician’s recommendation for prevention programs. With this recommendation, they can also take part in additional offers. All offers will be provided by exercise specialists from the statutory health insurance company and are based on their own manual, which are adhered to in a restrictive manner. Nutrition offers include: a workshop that focuses on education, particular recommended foods and the right combination of foods to induce positive health effects. It also highlights general principles of a balanced diet and practical tips, such that the knowledge can be implemented in the kitchen. The second offer, ‘body and soul in balance’, fosters active weight loss and mindful eating. The aim here is on sustainable change in diet, with more desire for exercise and fun within a lifestyle that relies on personal responsibility, knowledge and conscious decisions. The disease specific DMPs for CVDs include: ‘All the best for your heart’. This offer teaches the basics of avoiding and reducing coronary heart disease. ‘Fourfold increase in quality of life’ (DMP for DMT2) aims to increase everyday activities, giving information on avoiding obesity, recovery from physical and mental stress and information on special foot care for diabetes. Also, light gymnastics, light walking and a special strength-endurance training can be chosen. A focus of the general health offers is to reduce physical inactivity and to strengthen physical health resources. The offer includes courses to increase fitness, flexibility, endurance and strength. Included courses are: Clever-Walking, Fit-Mix, Functional Training, Easy Running, Outdoor Fitness, Back-Fit, and Back-Power.

### Process evaluation

The chosen pragmatic randomized controlled trial design is intended not only to evaluate the effectiveness of an intervention, but also to provide information on how the intervention works and how the intervention and its implementation in its specific context are influenced by various barriers and facilitating factors [69, 70]. Particularly for complex interventions such as *MultiPill-Exercise*, which are composed of multiple interacting components, determining the causes of change (primary action mechanisms) and identifying conditions for success (contextual factors) are key. Consequently, an accompanying process evaluation will be conducted with the aim of understanding not just if, but how and why an intervention has a particular effect, and which parts of a complex intervention have the greatest impact on outcomes [70, 71]. Thus, the process evaluation will help to understand the relationship between specific intervention elements and intervention outcomes, and will provide important information about key aspects that should be given special attention in the (successful) implementation of *MultiPill-Exercise* into regular health care [72]. For this purpose, implementation aspects from the perspective of therapists, participants, study sites and involved organizations will be identified in addition to the primary outcomes and mechanisms of action. Assessment procedures will be described in more detail in the following sections.

### Outcome measures

All participant-reported outcomes will be assessed using SecuTrial online questionnaires (InterActive Systems Berlin) at baseline and all follow-up time points. All physical performance measurements will be assessed on-site at t0, t6, t12 only (Fig. 3 and Table 2). The assessor team will consist of members of the study team, composed of employees of the university and university hospital, as well as a physician of the University hospital at t0. All assessors will be trained in advance and the examinations will follow the same order and predefined standard operating procedures (SOPs). Demographic data, clinical status (details of relevant history of disease, medical history, medications), history of exercise participation and outcome expectations are assessed in addition to primary and secondary outcomes. All on-site data will be directly entered to the electronic case report form (eCRF) using the software SecuTrial. The software automatically performs plausibility queries when the data is saved. The participants will receive E-Mails prior to the data collection, reminding them of the upcoming data collection.

#### Primary outcome measure

The retrospective European Health Interview Survey—Physical Activity Questionnaire (EHIS-PAQ) will be used to assess PA. The 8-item questionnaire covers physical activities during work, transportation, and leisure time, including sports activities, aerobic health enhancing activities and muscle-strengthening activities, over a typical week [73]. As an indicator that estimates compliance with the WHO aerobic PA guidelines, information on transportation-related PA (excluding walking) and leisure-time PA can be combined. The health enhancing physical activity (HEPA) Index [73] will be the primary outcome. EHIS-PAQ has acceptable reliability and moderate to strong validity for all domains other than moderate-to vigorous PA [74]. Clinical relevance is ensured by basing the outcome measure on (inter-) national physical activity recommendations.

#### Secondary and other outcome measures

##### Physical activity status

Further data from the EHIS-PAQ such as overall PA, including transport-related PA and especially the number of muscle-strengthening sessions, will be taken into account in order to analyze the fulfilment of health-oriented recommendations for aerobic PA and muscle strengthening activities (dichotomous outcomes: yes or no).

In addition to the self-report measure of PA, we will collect objective, device-based measurements of the physical activity status. For this, all participants will be asked to wear an accelerometer (wGT3X-BT Accelerometer) on a belt on the waist on the right hip during daytime for seven consecutive days after the on-site examinations [75, 76]. Participants will be included in the final analysis if at least three days of 10 h/day of wearing time is recorded. Instructions on handling of the device will be given by a trained research member. To return the device after the exposition week, a stamped and addressed envelope will be given to the participants.

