### Recruitment

The recruitment period will be 8 months and will be conducted in two waves due to organizational reasons related to the conduction of the intervention. In total, the *MultiPill-Exercise* intervention (IG) will be offered to 160 participants, while another 160 subjects will receive standard care (CG). Participants will be recruited via general practitioners and specialists (i.e. internal medicine, orthopedists, diabetologist, cardiologists) during regular consultations. The physicians will be informed beforehand about the study and the new health care offer *MultiPill-Exercise* by the staff of the health insurance company (Physician-Partner-System). In addition, exercise and nutrition specialists from the health insurance company will assist with recruitment by recommending these customers to get in contact with their physician in order to get a prescription, if applicable. Additionally, the commonly used media of the statutory health insurance company (advertisements in own or local magazines) will be used as well. Physicians prescribe the health care offer to potentially eligible patients (green prescription: this is a written recommendation of the physician for remedies that do not fall with budget, e.g., a therapy supplement or exercise advice) and also provide their patients with the study flyer, which includes contact details and other study related information, including a study homepage. If interested, participants contact the study examiners at the university hospital. Initial contact via telephone serves to inform potential participants on study contents, aims and the time-line of the study. Furthermore, inclusion and exclusion criteria will be checked. In case of potential eligibility, an appointment at the participant’s nearest study site will be made, where further information and written consent for the study will be obtained. For a sub-sample only, laboratory data (blood, urine) will be assessed. If interested and eligible, further consent will be acquired. At the study site, final checks for the inclusion and exclusion criteria will be undertaken by the study team. Participants who do not meet the inclusion criteria after the personal appointment are offered reference to the health insurance company's exercise specialists, who will provide them a different health service offer on a voluntary base. In the case of preliminary study inclusion, study-IDs are assigned. The IDs contain a number for the study center in addition to a sequential number. The subject then undergoes baseline medical examinations and physical performance tests. If no exclusion criteria are found during these examinations, the subject is considered to be fully included into the study and will be randomized into the study interventions as outlined below. Participants randomized into IG will be allocated to the *MultiPill-Exercise* intervention. They will immediately receive appointments and necessary information about the study from the study team. The participants of the CG will be assigned to the staff of the health insurance company, who will explain the possibilities of standard care at the particular study site to them. The standard care intervention will then be determined, taking into account the customer’s preferences. Details are depicted in the study flow-chart (Fig. 1).

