### Randomization

The study staff retrieve the study arm of a new subject online from the study software SecuTrial, a web-based database application for administrative, organizational and implementational support in clinical and epidemiological research projects, hosted by the statistical center of the study. For practical recruitment reasons, two identical intervention/control phases will be conducted at each of the study sites. For each phase and site, approximately *n* = 10 subjects will be allocated to IG and CG, respectively. As such, randomization will be generated in two sequences (= phase), each with eight strata (= study site) with random block lengths of four or six and a balanced allocation of *n* = 20. For each study site, a different randomization list will be generated, and a new randomization list will be used for the second study phase. Figure 2 displays the randomization process, explanatory for one organizational unit.

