**Overall**				
Participant’s characteristics	Date of birth, gender, ethnicity, BMI (height, weight), highest academic qualification (no degree, middle school, high school), labor situation (working, retired, unemployed in rehabilitation status), current profession, weight at birth, week of pregnancy at birth	SAQ	IG, CG	t0
Clinical status	Diagnoses of OA, Diabetes mellitus Type 2, Cardio vascular disease, and if applicable, date of initial diagnosis, in case of OA site (s) and joint (s) of OA diagnosis	SAQ, on-site CRF	IG, CG	t0
	Other diagnosed comorbidities	SAQ, on-site CRF	IG, CG	t0
	Current medication assessed via medication schedule and/or packaging. Also, pre-determined drugs are recorded via the IDB	SAQ IDB On-site CRF	IG, CG	t0, t6, t12
History of exercise participation	Athleticism during childhood and adolescence	SAQ	IG, CG	t0
Outcome expectations	Personal therapy expectations	SAQ	IG, CG	t0
**Primary Outcome measure**	**Clinical Outcomes**			
Physical activity status	Leisure-time physical activity in a typical week (EHIS-PAQ, HEPA Index [38])	SAQ	IG, CG	t0, t3, t6, t12, t18
**Secondary outcome measure**	**Clinical outcomes**			
Physical activity status	Work-related and transport-related physical activity in a typical week (EHIS-PAQ [38])	SAQ	IG; CG	t0, t3, t6, t12, t18
	Actigraph (wGT3X-BT Accelerometer) for 7 days	wGT3X-BT Accelerometer	IG, CG	t0, t6, t12
Health related quality of life	Veterans RAND 12 Item Health Survey (VR12), retrospective 4 weeks [39, 40]	SAQ	IG, CG	t0, t3, t6, t12, t18
Global health assessment	One Item, General Health, of the VR12 [39, 40] to assess global health [41]	SAQ	IG, CG	t0, t3, t6, t12, t18
Overall perceived benefit	Overall perceived satisfaction with the benefit of the intervention [42]	SAQ	IG, CG	t3, t6, t12, t18
Osteoarthritis specific outcomes	Hip Osteoarthritis Outcome Score (HOOS), Knee injury and Osteoarthritis Outcome Score (KOOS)	SAQ	IG, CG (only participants with OA)	t0, t3, t6, t12, t18
	Pain visual analog pain scale (0–10) [42, 43]	SAQ	IG, CG (only participants with OA)	t0, t3, t6, t12, t18
Cardio vascular risk status	10-year risk of myocardial infarction, PROCAM-Score short form [32]	SAQ	IG, CG	t0, t3, t6, t12, t18
Diabetes mellitus risk status	German diabetes risk score [30, 31]	SAQ	IG, CG	t0, t3, t6, t12, t18
Dietary intake	Food Frequency Questionnaire [44]	SAQ	IG, CG	t0, t3, t6, t12, t18

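### As written, the t0 accelerometer week is not placed before randomization and disclosure, yet its value would be the baseline covariate for the device outcome

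*Protocol article*

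**What the plan says.** Table 2 of the protocol article lists the device ("Actigraph (wGT3X-BT Accelerometer) for 7 days") as a secondary outcome in both arms at t0, t6 and t12. The Physical activity status section gives the timing for all three points in one phrase: it is worn "during daytime for seven consecutive days after the on-site examinations" and then returned by post. No visit at the end of the wear week is described.

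The Recruitment section gives the order of steps at entry. After preliminary inclusion, the participant has the baseline medical examinations and performance tests. The next step reads: "If no exclusion criteria are found during these examinations, the subject is considered to be fully included into the study and will be randomized". Of the intervention group it then says: "They will immediately receive appointments and necessary information about the study from the study team". For the control group it says: "The participants of the CG will be assigned to the staff of the health insurance company", with no interval stated.

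The Randomization section adds: "The study staff retrieve the study arm of a new subject online from the study software SecuTrial". It sets no condition about a finished device week. The Blinding section states that participants cannot be blinded.

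The Statistical analysis section has continuous secondary endpoints analysed like the primary one: ANCOVA where a baseline value exists, ANOVA otherwise, with results not confirmatory. It also plans to assess whether randomization succeeded by comparing the arms at baseline.

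**The concern.** A baseline covariate must be fixed before allocation, or at least before the participant can react to it. Here the examination comes first, allocation depends only on that examination, and the device week also starts after it. Nothing in the text makes allocation or disclosure wait for the seven days to pass. A participant who has just been told of an exercise programme, or of standard care, may behave differently while wearing the device.

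If so, the t0 value carries part of the treatment effect. Adjusting for it removes that part from the estimate, and a true early response could be read as baseline imbalance.

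The accelerometer is the only device-based measure of physical activity in the trial. Spiroergometry and the chair-stand test are objective but measure fitness and strength. The primary outcome is an unblinded self-report, so readers will look to the device for support. A later analysis plan can drop the covariate, but it cannot recover an uncontaminated baseline.

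**Working it through.** **The plan's own figure.** The Sample size section gives 123 evaluable participants per group for HEPA. A two-sample t-test with effect size 0.36, two-sided 0.05 and 80% power gives 122.09, so 123. The figure reproduces. It concerns the questionnaire and neither supports nor weakens this point. The documents give no planning figure for the accelerometer.

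**Order of events at t0, from the text.**
1. On-site baseline examination (Recruitment).
2. If no exclusion criterion is found, randomization (Recruitment), with the arm retrieved online (Randomization).
3. Intervention participants informed immediately after step 2; control participants passed to insurer staff, timing not given (Recruitment).
4. Seven days of device wear, starting after step 1 (Physical activity status).

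Steps 2–3 and step 4 both follow step 1, and no rule orders them against each other. The wear week is clean only if steps 2–3 are delayed by at least seven days, which the text does not require.

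**Effect on the ANCOVA.** Let D be the true between-arm effect at follow-up, b the within-arm slope of follow-up on baseline, and d the between-arm difference in the t0 wear week caused by knowing the arm.

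Adjusted effect = D − b×d

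With equal standard deviations at both times, b equals the correlation r. Writing d = f×D, where f is the share of the later effect already present in the wear week:

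Adjusted effect = D×(1 − r×f)

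Neither r nor f is in the documents; both are assumptions. Share of the true effect retained:

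| | f = 0 | f = 0.10 | f = 0.25 | f = 0.50 |
|---|---|---|---|---|
| r = 0.3 | 100% | 97% | 92.5% | 85% |
| r = 0.5 | 100% | 95% | 87.5% | 75% |
| r = 0.7 | 100% | 93% | 82.5% | 65% |

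Example: r = 0.5, f = 0.50 gives 1 − 0.5×0.50 = 0.75.

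**Simulation check.** With 123 per arm, r = f = 0.5 and D = 105/289 = 0.363 (the HEPA effect size, borrowed only as a scale), 3,000 runs gave a mean adjusted effect of 0.274. The formula gives 0.363×0.75 = 0.272.

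**Direction.** What counts is the difference between the arms. If both react equally, d = 0 and there is no bias. If control activity rises more than intervention activity, f is negative and the estimate is inflated: r = 0.5 and f = −0.25 give 1 + 0.125 = 112.5%. A t6 or t12 comparison that does not use the t0 device value is unaffected in every case.

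**The case against.** The strongest reply is that the documents never say that randomization falls on the examination day or within the following week. The word about immediacy describes what happens after allocation, not how soon allocation follows the examination, and for the control group there is no timing at all. Figs. 1 and 3 were not visible in the text reviewed, and they or the standard operating procedures may show a waiting period. This stands against any claim that participants certainly wear the device knowing their arm. A reader might infer that, but the text supports only the weaker statement that the described sequence implies it and nothing prevents it. The reply does not remove the point, because the article sets out the entry steps one by one and ends them in randomization with no device week in between.

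The second reply is that the consequence is small. The outcome is secondary and non-confirmatory, and with f = 0.10 between 93% and 97% of the effect is retained. That is right, and it limits the weight of the point. A reader might infer that the HEPA result is compromised or that the device result could not be interpreted at all. Neither follows: HEPA does not use the device value, and an unadjusted device comparison remains valid.

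Third, a reader might assume that the bias always runs toward no effect, or express it as a fraction of the 15 minutes per day that the Sample size section calls relevant. The control group also learns its arm and is offered exercise courses, so the direction is open. The 15 minutes refer to the questionnaire index, and the documents give no accelerometer threshold.

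**Conclusion.** The point holds in a limited form. As written, the protocol does not place the t0 accelerometer week before randomization and disclosure, and its sequence implies a device baseline that is wholly or partly post-allocation in an unblinded trial. Using that value as covariate would leave about (1 − r×f) of the true effect, 97% to 65% over the assumed ranges, or more than 100% if control activity rises more. These figures rest on assumed r and f, equal variances at t0 and follow-up, and a simple mean shift in the wear week. They show sensitivity and do not estimate what will happen.

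Only baseline-adjusted or change analyses of the accelerometer outcome, and its use as a check on randomization, are touched. The change is worth making because a clean baseline cannot be restored afterwards. If current practice already holds allocation back, one clarifying sentence settles the matter.

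**What to change.** State in the protocol that the arm is retrieved from SecuTrial, or at least disclosed to the participant, only after the seven-day t0 wear period has ended. Tie the release to the end of the wear period and not to postal return of the device, so that mail delays do not hold up entry. Record the wear dates and the disclosure date.

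Where the device was worn after disclosure, do not use that t0 value as a covariate or as evidence on the success of randomization. Compare the arms at t6 and t12 without it, keeping study site and recruiting phase in the model. The plan already provides ANOVA for endpoints without a baseline. If disclosure timing differs between arms, make this choice for the whole comparison and not participant by participant.

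The main cost is about one week between examination and disclosure, with no new measurement. Giving up the covariate costs precision: residual variance rises by a factor 1/(1 − r²), which is 1/0.91 = 1.10 at r = 0.3, 1/0.75 = 1.33 at r = 0.5 and 1/0.51 = 1.96 at r = 0.7. That is a reason to prefer the delay.
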